#### Profiling circulating cytokine from liquid biopsies

We will measure cytokines known to be associated with inflammation, angiogenesis, and growth processes using a membrane-based Human Cytokine Antibody Array kit according to the manufacturer’s instructions.

#### Panel of immune-related genes and signatures expression analysis (non-exhaustive list)

DEG analysis between responders and non-responders to anti-PD1/PD-L1 immunotherapy will be performed including:IFN-γ mediated signalingStimulatory (CD27, CD28, CD40, OX40, glucocorticoid-induced TNFR-related protein (GITR), inducible costimulator of T cells (ICOS),…) and Inhibitory (PD1, B7-H3, B and T lymphocyte attenuator (BTLA), cytotoxic T lymphocyte antigen 4 (CTLA-4), indoleamine 2,3-dioxygenase (IDO), killer cell immunoglobulin-like (KIR), lymphocyte-activation gene 3 (LAG3), T-cell immunoglobulin and mucin domain 3 (TIM3), V-domain Ig suppressor of T cell activation (VISTA),…) immune checkpoint genesHypoxia-related genes (Hypoxia-inducible factor (HIF)-1α; HIF-2α,…)ΔNp63 (p40) gene expression signatureImmune cell gene signaturesImmunogenic cell death (Calreticulin, p-eukaryotic initiation factor 2α (eIF2α),…) and mitophagy-related markers (Bcl-2 interacting protein 3 (BNIP3),…)

### Medical data collection

The following data will be collected for each patient to correlate biological data with clinical response, at the time of inclusion and during medical follow-up: demographic and clinical data (age, sex, weight, height, performance status,…), medical history, lines of treatment, clinical evaluation, and imaging reports. All data will be recorded in the Case Report Form (CRF) (CleanWebTM, Copyright ©2023 Telemedicine Technologies).

### Statistical analysis

Primary endpoint will be the measure of response to PD-1 checkpoint blockade (overall response, CR, and PR) in patients with IFN-γ–related gene expression signature. The expected response rate in patients with IFN-γ–related gene expression signature is 60%, the expected two-sided alpha error is 0.05 and beta error is 0.2, the required number of patients is calculated to be 54 based on the exact binomial test (Casagrande et Pike) and considering the patients excluded from the analysis due to censoring. DEG analysis between responders and non-responders will be performed using DESeq2 package. IFN-γ–related gene expression signature and other genes include in the panel will be considered differentially expressed if log 2-fold change is at least ± 2 and *p*-adjusted value ≤ 0.05.

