### Study objectives and endpoints

The main objective of this study is to identify effective biomarkers of response to PD-1 checkpoint blockade using combinatorial omics analysis including spatial transcriptomics, scRNA-seq, and miRNomics. The primary endpoint is the prospective validation of the IFN-γ–related gene expression signature to predict response to PD-1 checkpoint blockade (overall response including complete response (CR) and partial response (PR)). Tumor response was defined according to the Response Evaluation Criteria In Solid Tumor (RECIST) criteria. Secondary outcomes are the prospective validation of potential response biomarkers (immunogenic cell death and mitophagy-related markers, expression of hypoxia-related markers, and circulating miRNA-mediated immunomodulation). Exploratory outcome measures will include dynamic and differential profiling of the immune repertoire in the TME between responders and non-responders.

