## Discussion

Immune checkpoint inhibitors of PD-(L)1 represent a significant breakthrough in the treatment of HNSCC in the R/M setting because of the prolonged responses observed with a near doubling of the 2-year survival in the Keynote-048 study. However, response rates remain < 20% with life-threatening progression, even hyperprogression occurring in as much as 30% of the cases in some studies, resulting in excess mortality observed in the initial part of the immunotherapy arms survival curves [46]. The increase of this response rate requires new immunomodulatory agents and the development of effective biomarkers to support a better selection of patients most suitable for immunotherapy. But the last few years have seen a number of failures in clinical drug development for HNSCC, which may reflect an incomplete understanding of the TME including the molecular and cellular drivers of immune escape. In this study, we consider the understanding of the dynamic evolution of TME under immune checkpoint inhibitors to be of crucial importance. This will be accomplished through the emergence of breakthrough technologies including scRNA-seq and spatial transcriptomics (performing a deep analysis with cellular resolution of the main cellular subsets), and the anatomical localization of HNSCC allowing for multiple biopsies during the treatment. However, we realize that the main limitation of this study is the TME heterogeneity. Indeed, a single tumor sample may not be representative of the immune infiltration landscape if, for example, the same tumor has both “immune cold” and “immune hot” regions which could affect up to a third of the patients [26]. Complementary approaches such as liquid biopsy could help overcome this problem, and will be included in this study to focus on the exploration of circulating miRNA-mediated immunomodulation and circulating cytokines.

In this single-center prospective study, we will study biological samples of patients undergoing anti-PD-1 immunotherapy to generate effective biomarkers to define the optimal therapeutic strategy and identify potential new immunomodulatory targets in patients with R/M HNSCC.

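### The primary endpoint is response in signature-positive patients, but the only criterion stated for the signature is a responder versus non-responder contrast that labels no patient

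*Protocol article*

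**What the plan says.** The protocol article states the primary endpoint twice. Under *Study objectives and endpoints*: "The primary endpoint is the prospective validation of the IFN-γ–related gene expression signature to predict response to PD-1 checkpoint blockade". The *Statistical analysis* section words it differently: "Primary endpoint will be the measure of response to PD-1 checkpoint blockade (overall response, CR, and PR) in patients with IFN-γ–related gene expression signature".

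Next comes the design assumption: "The expected response rate in patients with IFN-γ–related gene expression signature is 60" per cent, with "the expected two-sided alpha error is 0.05 and beta error is 0.2" and a total of 54 patients.

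The same paragraph then turns to gene expression: "DEG analysis between responders and non-responders will be performed using DESeq2 package". The IFN-γ signature and the other panel genes count as differentially expressed at a log2 fold change of at least ±2 with adjusted p ≤ 0.05. The sections on spatial transcriptomics and on the gene panel describe the same contrast. The panel lists IFN-γ signalling as one item and is declared not exhaustive.

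The only method for a patient-level cut-off is in the section on circulating miRNA. It is a ROC analysis against response, and it concerns a secondary marker.

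**The concern.** A response rate among signature-positive patients needs a count of such patients. That count should be fixed by a rule that can be applied to a pre-treatment sample before anyone knows how the patient fared. The printed criterion works in the other direction: it sorts patients by response and asks which genes differ.

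The stated analysis and the stated endpoint therefore do not meet. The analysis could be carried out in full and the response rate among positives would still be unknown. If the gap were closed late, by choosing genes or a threshold once responses are in hand, the reported rate would be biased upwards and could not count as validation.

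**Working it through.** **1. Inputs.** From *Statistical analysis*: 60% response in positives, two-sided alpha 0.05, beta 0.2, 54 patients. From *Discussion*: "However, response rates remain < 20" per cent. From *Background*: an objective response rate of 23.3% with pembrolizumab alone at CPS ≥ 20. Not given: the comparator rate, the share of positives and the exclusion rate.

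**2. What each quantity needs.**

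| | Stated endpoint | Stated criterion |
|---|---|---|
| Form | r₊ / n₊, responders among positives | log2(mean in responders / mean in non-responders), per gene |
| Conditions on | the marker | the response |
| Output | one proportion | one yes/no per gene or signature, for the cohort |
| Available | once positives are labelled | only after response is known |

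A fourfold difference in group means (log2 = 2) yields neither n₊ nor r₊. No step in the article leads from the second column to the first.

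**3. The plan's figure of 54.** It cannot be derived from the stated inputs alone. With an assumed 20% in negatives and equal groups, the Casagrande–Pike formula gives:

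- n′ = [1.96·√(2×0.4×0.6) + 0.842·√(0.24+0.16)]² / 0.4² = 22.33
- n = (n′/4)·[1 + √(1 + 4/(n′×0.4))]² = 27.1 per group, or 54.2 in total (56 when each group is rounded up)

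At an assumed 19% the rounded total is 52; at 23.3% it is 66. A single-arm exact test of 60% against an assumed 40% needs 55 patients, all of them positive. So 54 may mean about 27 positives and 27 negatives, or 54 positives. Under either reading the sample size depends on a patient label that the printed criterion does not supply.

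**4. What the plan's own rates allow.** Let o be overall response, q response in negatives and π the share of positives. Then o = 0.60π + q(1 − π), so π = (o − q)/(0.60 − q). For 54 patients:

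| Overall response o | q = 0 (upper limit) | q = 10% (assumed) |
|---|---|---|
| 20% | 0.20/0.60 = 33.3%, 18 positives | 0.10/0.50 = 20%, 10.8 positives |
| 23.3% | 0.233/0.60 = 38.8%, about 21 positives | 0.133/0.50 = 26.6%, 14.4 positives |

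An upper-tertile cut (18 of 54) sits on the limit at 20%: 18 × 0.60 = 10.8, which is every responder (0.20 × 54 = 10.8), leaving none among the 36 negatives. If negatives responded at 20%, overall response would be (10.8 + 7.2)/54 = 33%. The equal-group reading in step 3 implies (16.2 + 5.4)/54 = 40% overall, above both rates in the article.

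**5. If status were fitted to response.** For illustration, take a marker with no association, 54 patients and 20% response. One simulation with a cut chosen on the same responses gave Fisher p ≤ 0.05 in 23% of runs and a mean response of 32% in the so-called positives. With the direction fixed in advance and the cut maximising sensitivity plus specificity, 4,000 simulated cohorts gave 13% and 31%. The size depends on how the cut is chosen; the direction of the bias does not.

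**The case against.** The strongest reply is that this is a condensed article. The full protocol or analysis plan may name the signature, its score and its cut-off. The article also writes of the signature with a definite article, as of something already specified. That stands, and a missing gene list would not by itself be a finding. What remains is a mismatch in the printed text: the criterion given for the primary marker does not yield the primary endpoint stated in the same paragraph.

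A reader might infer that the plan defines signature-positive patients through the DESeq2 result and is therefore circular. The article does not say so. It says when the signature counts as differentially expressed, which tests a group difference and assigns nobody a status. Circularity is conditional on that use, or on carrying the ROC method over from miRNA.

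A reader might also infer that 60% is out of reach because a median split allows at most 10.8/27 = 40% (47% at 23.3% overall). No section proposes a median split, so this shows no error.

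The background rates fit only loosely. The *Abstract* and *Background* use the figure below 20% for lasting responses, and only the *Discussion* applies it to response rates. The 23.3% comes from a selected subgroup. Neither is stated as the expected rate in this cohort, and the 54 already includes an unstated allowance for exclusions.

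**Conclusion.** The point holds on the printed text. The only criterion given for the IFN-γ signature is a cohort-level contrast of groups formed by the outcome. It cannot identify the patients in whom a 60% response is expected, and it is not prospective validation. The text does not establish that status will be fitted to response, or that no patient-level rule exists elsewhere.

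The limit of about 18 to 21 positives assumes that overall response of 20% to 23.3% applies to all 54 patients and that no negative responds. With any response among negatives the limit falls, for example to about 11 to 14 at an assumed 10%. The simulated error rates rest on assumed inputs and only illustrate the risk. Because this is the primary endpoint, it should be settled before response data are joined to expression data.

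**What to change.** - Make the primary analysis response (CR + PR) by signature status.
- Take status from one IFN-γ score per patient, measured on the pre-treatment biopsy, with a fixed gene list, formula and cut-off. If a signature already exists, cite it and use its own cut-off. Otherwise set the cut-off without response data.
- Lock all three, with a date, before response data are merged.
- Keep the DESeq2 contrast of responders and non-responders as exploratory gene discovery.
- State the expected share of positives and the comparator rate behind the 54, and check the cut-off against the equation in step 4. An upper-tertile cut is a limiting case there, not a recommended value.

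The cost is protocol or analysis-plan wording and one data-lock step, with no new samples. The small downside is that the cut-off can no longer be tuned to the results.

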#### Tumor analysis by spatial transcriptomics and single cell RNA-seq

Spatial transcriptomics will be performed on FFPE tissue sections using the 10X Genomics Visium Spatial Gene Expression platform (10X Genomics, GenomEast, IGBMC, Illkirch, France). Histological sections will be stained using hematoxylin and eosin (H&E) to select the most relevant areas for analysis. Using a Leica RM2235 microtome (Leica, Nanterre, France), tissue sections will be cut from FFPE tissue blocks and placed within the etched frames of the capture areas on the active surface of the Visium Spatial Slide using the Visium CytAssist. The slide will be dried in an oven overnight at 37 °C and then at 60 °C for 25 min before dehydration in ethanol and H&E staining. The slide will finally be transferred to water and mounted in 87% glycerol before image acquisition on the same day. Image mosaic of each section will be acquired to generate a brightfield image of each section including the fiducial marker frame. Subsequently, stained sections will be processed as described in the demonstrated protocol “Visium Spatial Gene-Expression Reagent kits for FFPE, UserGuide” (CG000407). This kit enables spatial quantification of the expression of approximately 18,000 genes on FFPE tissue sections using a pair of specific probes for each targeted gene. Slides containing 4 capture zones will be used. Each 6.5 × 6.5 mm capture zone contains ~ 5,000 spots, and each spot is covered with capture probes bearing a unique barcode, known as a spatial barcode. Quantification and quality control of the final libraries will be performed using Bioanalyzer 2100 (Agilent Technologies, Santa Clara, United States).

Libraries will be sequenced on an Illumina NextSeq 2000 platform as paired-end 28 + 50 bases reads. Sequencing data will be processed using the Space Ranger software (10 × Genomics) for analyzing and visualizing spatial gene data produced by the 10 × Genomics Visium Platform including detection tissue, alignment reads, generation of read counts matrices, clustering and gene expression analysis, and place spots in spatial context on the microscope slide image. Differentially expressed gene (DEG) analysis between responders and non-responders will be performed using pseudo-bulking on DESeq2.

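### The IFN-γ signature has no multiplicity family of its own: one DESeq2 adjusted-p rule covers it and an open panel, which costs its differential-expression result power and stability

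*Protocol article*

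**What the plan says.** Study objectives and endpoints makes prospective validation of the IFN-γ signature as a predictor of response the primary endpoint. Statistical analysis words it as a response measure: "Primary endpoint will be the measure of response to PD-1 checkpoint blockade (overall response, CR, and PR) in patients with IFN-γ–related gene expression signature". The trial is sized on that response: "the required number of patients is calculated to be 54 based on the exact binomial test (Casagrande et Pike").

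The same section then gives the only rule for judging expression. DESeq2 compares responders with non-responders, and the IFN-γ "signature and other genes include in the panel will be considered differentially expressed" when the absolute log2 fold change is at least 2 and the adjusted p is at most 0.05. The tests over which p is adjusted are not named.

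Two candidate families appear elsewhere. The spatial transcriptomics section says of the assay: "This kit enables spatial quantification of the expression of approximately 18,000 genes on FFPE tissue sections". The panel section is headed "Panel of immune-related genes and signatures expression analysis (non-exhaustive list"), several of its entries end in ellipses, and it names no member genes for IFN-γ signalling.

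**The concern.** An adjusted p-value has meaning only relative to the set of tests it is adjusted over. The stated rule puts the primary biomarker and the exploratory genes in one set, and both sets the article offers reach well beyond the signature. One is the matrix given to DESeq2, which the software by default adjusts over in full apart from genes it filters out. The other is a panel whose membership is not closed.

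Two things follow. The signature genes pay for tests that have nothing to do with the IFN-γ hypothesis. And identical IFN-γ data can be called differentially expressed or not according to how many other genes are included and how many of those differ. A signature singled out in advance for validation should be exposed to neither.

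**Working it through.** **Inputs from the article.** 54 patients; response rates below 20% (Discussion); about 18,000 genes assayed; adjusted p ≤ 0.05; absolute log2 fold change ≥ 2.

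**The plan's own figure.** The 54 belongs to the binomial calculation and cannot be rebuilt from stated inputs, because no comparator rate is given. If 20% against 60% is assumed, an exact Fisher test with 27 per group has power 0.802, a total of 54. That calculation does not involve the adjusted p.

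**Assumptions not in the article.** 20% responders, 0.20 × 54 = 10.8, so 11 against 43; a 20-gene IFN-γ list with 10 true differences; independent genes; Benjamini-Hochberg adjustment; other true differences of the same size; panels of 100 or 200 genes.

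**Step 1, precision.** SE of a standardised difference = √(1/11 + 1/43) = 0.338. A true difference of 1.0 gives an expected test statistic of 1.0/0.338 = 2.96.

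**Step 2, simulated power per true gene on adjusted p alone, difference 1.0.** The two columns differ in whether the variance is treated as known or estimated (52 df).

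| Family | Normal reference | t reference |
|---|---|---|
| 20-gene list alone | 73% | 71% |
| Panel of 100; 0 / 20 others differ | 48% / 65% | 32–60% over all panel settings |
| Panel of 200; 0 / 20 / 45 others differ | 37–40% / 56% / 64% | (as above) |
| 18,000; 900 / 180 / 0 others differ | 37–39% / 17–18% / 5% | 27% / 11% / 3% |

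A rerun for this write-up agreed with both columns to within about 2 points.

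**Step 3, other effect sizes (normal reference).** At 1.2: 89–91% within the list, 66–85% in the panels, and 66% / 45–46% / 17–18% over 18,000. At 0.8: 43–47% within the list, 16% in a 200-gene panel with no other difference, and 9–11% / 2–3% / 1% over 18,000.

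**Step 4, adding the fold-change cut.** A gene sitting exactly at log2 fold change 2 has a test statistic of 2/(SD × 0.338):

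- SD 1: 5.92
- SD 1.5: 3.95
- SD 2: 2.96

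Even the strictest threshold over 18,000 genes, 0.05/18,000 = 2.8 × 10⁻⁶, needs a t of about 5.26 on 52 df. The consequences by SD are:

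- **SD 1.** A gene that clears the cut will usually clear any family as well. At standardised difference 1.0 the joint rule passes about 0.2% whatever the family.
- **SD 1.5 (true log2 difference 1.5).** About 16% pass with the list. Over 18,000 genes, 15–16% pass if 900 others differ. If 180 differ, the figure is about 15% with the normal reference and about 9% with the t reference in the rerun. If none differ it cannot exceed the 3–5% that pass on adjusted p.
- **SD 2 (true log2 difference 2).** 47–51% pass with the list, against 30–37%, 11–18% and 3–5% over 18,000 genes with 900, 180 and 0 others different.

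**The case against.** The strongest reply is that the adjusted p does not decide the primary question. That stands. The primary endpoint is response in signature-positive patients, sized on an exact binomial test at two-sided 0.05. A reader might infer that the DESeq2 rule is the confirmatory test, or that a false-discovery rate contradicts the stated alpha. The article supports neither, because these are two different analyses.

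It is also fair that no text says p is adjusted over 18,000 genes. That number is assay coverage, and the panel is at least as natural a reading. The loss does not depend on the larger family, however: a panel of 200 with nothing else different roughly halves power at a difference of 1.0.

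A reader might further infer that most real differences among pre-specified primary genes will be missed. No such genes are listed, and the claim fails in several settings: 66% are still found over 18,000 genes at a difference of 1.2 when 900 others differ. For true log2 differences below 2, the fold-change cut is often the tighter limit, and changing the family may then gain little.

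Finally, family membership and a locked gene list are usually left to the analysis plan, and a condensed article need not give them. Their absence is not the point here. The point is the rule the article does state, which treats the primary signature and the other panel genes alike.

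**Conclusion.** The concern holds for the differential-expression result of the IFN-γ signature, and for that result only. Under either reading of the family, the signature is adjusted alongside unrelated exploratory genes, and its result depends on how many there are and how many differ.

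The direction of the loss is clear; its size is not fixed by the article. The gene SD, the effect size, the list length and the share of other genes that differ are all assumed. On adjusted p alone the loss ranges from modest (73% to 65% in a 100-gene panel with 20 other differences) to near total (71% to 3% over 18,000 with none). With the fold-change cut kept, it is negligible at SD 1, small at SD 1.5 unless few other genes differ, and material at SD 2 or more. The change should be made because it is nearly free. It is not a threat to the sized primary test.

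**What to change.** 1. Lock the IFN-γ gene list before response data are linked, and adjust p within that list only. Alternatively, test one pre-defined signature score at two-sided 0.05.
2. Close each secondary list (immunogenic cell death and mitophagy, hypoxia) and treat it as its own family.
3. Keep transcriptome-wide adjusted p-values for results labelled exploratory.
4. State that this rule governs the differential-expression result and is separate from the exact binomial test of response.

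The cost is wording, an early decision on list membership and one extra adjustment step, with no new patients, samples or assays. The downside is small: signature and panel p-values no longer carry transcriptome-wide control and should be reported as such. The change does not deal with the fold-change cut, which will still limit detection of true log2 differences below 2.
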